#### Mediational analyses

We will examine whether the effect of treatments on outcomes at 12-month follow-up are mediated through changes in “*process variables*” (mindfulness, pain catastrophising, psychological inflexibility, and self-compassion) at post-treatment. Using two-stage meta-analytic structural equation modelling, Gu and colleagues [89] identified moderate and consistent evidence for some of the proposed process variables [mindfulness and rumination (dimension of catastrophising)] and preliminary but still insufficient evidence for others [self-compassion and psychological flexibility] as mediator mechanisms underlying standardised MBIs (MBSR and MBCT). Following Luciano et al. [87], pre- to post-treatment change scores for the process variable, and the pre- to follow-up change scores for the outcome variables will be computed. We will analyse the direct and indirect relationships between treatments (TAU + MBSR vs. TAU + FibroQoL), process variables, and study outcomes using path analysis models. The treatment condition is considered the independent variable, the pre-post change scores in the process variables are the mediators, and pre- to follow-up changes in the outcome variables are the dependent variables. In this way, we are taking temporality into account, which increases the prospect of establishing conclusions about causality. We will analyse the data of participants from the MBSR and FibroQoL treatments who receive a sufficient dose of the intervention, defined in this case as attendance at a minimum of 6 of the 8 weekly sessions. Simple and multiple mediation (simultaneously testing multiple variables as mediators) models will be computed. The direct path between study condition and clinical outcome and the indirect effect through the process variables will be tested.

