### Procedure

The potential FMS participants will be screened through an initial telephonic interview by one of the authors ([name]), who will provide a general overview of the study. Subsequently, two highly trained clinical psychologists (not involved with the treatment and blind to group allocation) will make an appointment with those patients who met the inclusion criteria and agreed to participate in the study. The psychologists will check all inclusion/exclusion criteria (both general and additional for the biomarkers study) and will perform all face-to face interviews. As mentioned above, study participants will be randomised to one of the three conditions (i.e., TAU, TAU + MBSR, TAU + FibroQoL). Both MBSR and FibroQoL are conducted in a group format (up to 15 people in each group). To balance the number of participants eligible for the biomarkers sub-study across the three arms, stratified randomisation will be performed. The proportion of eligible participants for the biomarkers evaluation and those only meeting criteria for the general study will be pre-fixed at 1:1 in all samples. Four treatment waves (*N* = 45 each) will be carried out to achieve the required final sample (*N* = 180).

Three-five days after the clinical evaluation, patients assigned to the biomarkers sub-study will be contacted for blood extraction and MRI completion. To minimise circadian variability in immunological markers, all whole blood samples will be collected between 8–9 am. Interventions will be conducted using a parallel design to reduce seasonal variability in the study measures. The participants will be interviewed at baseline, after treatment, and at 12-month follow-up (56 weeks after randomisation). The neuroimaging tests and cytokine measurements will be performed at baseline and after treatment. A flowchart of participants is displayed in Fig. 1.

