### Study measures

Study participants will complete the following instruments as part of a paper-and-pencil battery of measures (see Table 3):*Sociodemographic-clinical questionnaire*. The following information will be collected: gender, age, ethnic group, marital status, living arrangements, educational level, employment status, and annual income. Relevant clinical variables, such as family and personal medical history, years of FMS diagnosis and comorbid conditions will also be assessed.

**Table 3 Tab3:** Study periods at which measures and data are collected

Study measures	Baseline	During treatment	2 months	12-months
Demographic information (gender, age, etc.)	X			
History of FMS (years of illness)	X			
Contact details	X			
SCID-I (depression module)	X			
*Screening measures*				
MMSE (cognitive impairment)	X			
*Primary outcome measure*				
FIQR (functional impairment)	X		X	X
*Secondary outcome measures*				
FSDC (fibromyalginess)	X		X	X
HADS (anxiety and depression)	X		X	X
PSS-10 (perceived stress)	X		X	X
MISCI (subjective cognitive impairment)	X		X	X
EQ-5D-5L (quality of life)	X			X
CSRI (health economic evaluation)	X			X
FFMQ^a^ (mindfulness facets)	X		X	X
PCS^a^ (pain catastrophizing)	X		X	X
PIPS^a^ (psychological inflexibility)	X		X	X
SCS-12^a^ (self-compassion)	X		X	X
*Other measures*				
Structural + Functional Neuroimaging data	X		X	
Inflammatory data	X		X	
CEQ (Expectation/Satisfaction with treatment)	X (EXP)		X (SAT)	
PGIC & PSIC (Impression of change)			X	X
Treatment attendance form: Attendance at each scheduled MBSR/FibroQoL session		X		
Log of MBSR and FibroQoL practices		X		
Treatment fidelity (review of video-taped MBSR sessions) & monitoring of adverse events		X	X	X

*CEQ* Credibility/Expectancy Questionnaire, *CSRI* Client Service Receipt Inventory, *EQ-5D-5L* EuroQoL questionnaire, *FFMQ* Five Facet Mindfulness Questionnaire, *FIQR* Revised Fibromyalgia Impact Questionnaire, *FSDC* Fibromyalgia Survey Diagnostic Criteria, *HADS* Hospital Anxiety and Depression Scale, *MISCI* Multidimensional Inventory of Subjective Cognitive Impairment, *MMSE* Mini-Mental State Examination, *PCS* Pain Catastrophizing Scale, *PGIC & PSIC* Patient Global and Specific Impression of Change, respectively, *PIPS* Psychological Inflexibility in Pain Scale, *PSS-10* Perceived Stress Scale, *SCID-I* Structured Clinical Interview for DSM Axis I Disorders, *SCS-12* Self-Compassion Scale

^a^Secondary outcome measures that also considered process variables

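### The mediation outcome change (baseline to 12 months) contains the mediator window (baseline to post-treatment), so the temporality sentence claims more than the change-score model supports

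*Protocol article*

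**What the plan says.** The section Mediational analyses in the protocol article states the scores to be used: "pre- to post-treatment change scores for the process variable, and the pre- to follow-up change scores for the outcome variables will be computed". In the path model, "the pre-post change scores in the process variables are the mediators" and "pre- to follow-up changes in the outcome variables are the dependent variables". The next sentence draws the inference: "In this way, we are taking temporality into account, which increases the prospect of establishing conclusions about causality".

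The model covers the two active arms only. It examines "direct and indirect relationships between treatments (TAU + MBSR vs. TAU + FibroQoL), process variables, and study outcomes using path analysis models", in patients who reach "attendance at a minimum of 6 of the 8 weekly sessions".

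Table 3 (Study measures) schedules FIQR, FSDC, HADS, PSS-10 and MISCI at baseline, 2 months and 12 months. The four process measures (FFMQ, PCS, PIPS, SCS-12) are taken at the same visits. EQ-5D-5L is scheduled only at baseline and 12 months. The mediation section makes no use of the 2-month outcome values.

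**The concern.** The opening words of the temporality sentence rest the claim on the choice of these two change scores. Because both start at baseline, the outcome score includes everything that happened to the outcome while the mediator was changing. If mindfulness and FIQR improve together during the eight weeks, or FIQR improves first and mindfulness follows, the path from mediator to outcome is non-zero even when post-treatment mindfulness has no influence on later FIQR.

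What is at stake is the third objective. The trial could report a process variable as a mechanism of long-term improvement when the data show only that the two moved together. Some co-movement is plausible, since process and outcome measures are self-reports completed at the same visits.

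**Working it through.** The mediation section gives no figure, so there is none to reproduce. The overlap follows from the definitions; the simulations only show how large its effect could be.

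**Step 1. Definitions.** Let M be the mediator and Y the outcome, at baseline (0), post-treatment (1) and 12 months (2).

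- Mediator score: ΔM = M1 − M0.
- Outcome score: ΔY = Y2 − Y0 = (Y1 − Y0) + (Y2 − Y1).
- Planned mediator-to-outcome path: b = [Cov(ΔM, Y1 − Y0 | arm) + Cov(ΔM, Y2 − Y1 | arm)] / Var(ΔM | arm).

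The first covariance is change over the same window. Only the second has the mediator change before the outcome change. The planned b adds them together.

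**Step 2. Inputs.**

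- From the document: two arms; 60 per arm with 20% maximal attrition (Participants), so 60 × 0.8 = 48 per arm.
- Assumed, not in the document: baseline SD 1; stability 0.7 per interval; baseline correlation of M and Y −0.4; residual variance 1 − 0.7² = 0.51; residual correlation of M1 and Y1 of size r in the improving direction; arm difference at post-treatment 0.5 SD on M and, separately, 0.5 SD on Y. Y2 depends only on Y1, so M has no effect on Y.

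**Step 3. Expected values.**

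- Cov(ΔM, ΔY | arm) = (0.7 − 1)(0.49 − 1)(−0.4) − 0.7 × 0.51 × r = −0.0612 − 0.357r.
- Var(ΔM | arm) = 0.3² + 0.51 = 0.60.
- Apparent indirect effect = 0.5 × b; total effect = 0.7 × (−0.5) = −0.35.

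| r | b | apparent proportion mediated | false mediation, planned model (simulated) |
|---|---|---|---|
| 0 | −0.102 | 0.15 | 11% |
| 0.2 | −0.221 | 0.32 | 32% |
| 0.4 | −0.340 | 0.49 | 65% |
| 0.6 | −0.459 | 0.66 | 83% |

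Rates come from 2,000 simulated trials per setting, with both paths required to be significant at two-sided 0.05. A lagged model (Y2 on arm and M1, adjusted for M0, Y0 and Y1) gives 4–5%. The 11% at r = 0 arises because both scores subtract baselines that are themselves correlated.

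**Step 4. A second, simpler model.** It models changes directly: 0.53 SD arm difference on both early changes, carry-over c of early outcome change to 12 months, independent late change with SD 0.7. The expected spurious indirect effect is 0.53 × c × r. For c = 0.8 and r = 0.3 that is 0.127; the simulation gave 0.126, significant in 43% of runs at 48 per arm. Over c = 0.5 to 1.0 the rate is 29–48% at r = 0.3 and 59–71% at r = 0.5. At 60 per arm it is 39–64% and 75–82%, so a larger sample does not help. At r = 0 it is 3–4%. Adding the post-treatment outcome brings the rate to about 3–4% in every setting.

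**Step 5. Dependence on the arm difference in the mediator.** In the Step 2 model at r = 0.4, the false rate is 65% for a 0.5 SD difference, 17% for 0.2 SD and 7% for 0.1 SD. Both paths must be significant, so a small difference between MBSR and an active comparator limits how often mediation is declared.

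**Step 6. The lagged model under true mediation.** If M does drive Y, but entirely within the treatment period (slopes 0.5 to 1.0), the planned model finds it in 74–88% of trials and the lagged model in only about 4–5%. Y1 then lies on the causal path, and adjusting for it removes the effect.

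**The case against.** Four points can be made for the plan.

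- **The claim is hedged and the ordering is partly real.** The protocol says only that the prospect of causal conclusions is increased, and the mediator is measured months before the endpoint at 56 weeks. This stands. A reader might infer that the plan has no temporal ordering at all; that is not so. The ordering of measurements is real, but it does not settle the ordering of changes.
- **The scores fit the stated question.** Total improvement from baseline to 12 months is a legitimate outcome, and the lagged model answers a different question: mediation of later change. This stands, and Step 6 shows the price. A reader might infer that every causal statement should rest on the lagged model alone. That does not follow, because it would turn a genuine mechanism completed during treatment into a null result.
- **The size is assumed.** The document gives no correlations, stabilities or mediator effects, the comparator is active, and the attendance rule may leave fewer than 48 per arm. This stands, so the percentages are illustrations over a range. The residual correlation in the simulations is also a form of mediator-outcome confounding, which limits mediation analysis generally.
- **This is a condensed article.** Covariates and further paths may be in an analysis plan that is not shown. That would excuse silence on a lagged path. It does not cover the temporality inference, which the article states and ties to the two change scores.

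**Conclusion.** The point holds in a limited form. The outcome window contains the mediator window by definition, so the two change scores cannot separate mediator-first change from simultaneous or outcome-first change, and the temporality sentence goes further than the model allows.

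How often this would mislead is uncertain. Under the Step 2 assumptions it ranges from 7% of trials (arm difference 0.1 SD, correlation 0.4) to 83% (0.5 SD, correlation 0.6). A reader might infer that a false mediation finding is the likely result in this trial; the documents do not support that, because neither the correlation nor the MBSR-versus-FibroQoL difference on the mediators is given.

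The point concerns the third, explanatory objective. It does not touch the primary FIQR comparison. It should be corrected before the mediation results are interpreted.

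**What to change.** 1. Keep the change-score path model, describe it as an analysis of association with total 12-month improvement, and withdraw the temporality and causality inference from it.
2. Add a lagged model: 12-month outcome on arm and post-treatment mediator, adjusted for baseline mediator, baseline outcome and post-treatment outcome. Fit it for FIQR, FSDC, HADS, PSS-10 and MISCI. It is not available for EQ-5D-5L, which has no 2-month value.
3. Report both models. Claim that mediator change precedes outcome change only where the lagged model supports it.
4. State that a null lagged result does not rule out mediation completed during treatment, and that neither model removes unmeasured mediator-outcome confounding.

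The cost is one further analysis on data already scheduled and a rewording of one sentence. The drawback is that the two models may disagree. The text should then say that they address different questions, total improvement and later change.

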First, we will use a micro-costing approach, which involves careful specification of training costs, staffing costs, venue overheads, materials, and staff travel. Then, following the International Society for Pharmacoeconomics and Outcomes Research (ISPOR) core recommendations for cost-effectiveness analyses alongside RCTs [91], we will calculate the incremental cost-utility ratios, defined as the difference in mean costs divided by the difference in mean QALYs. As the duration of the study is 12 months, neither costs nor outcomes are subject to discounting. QALYs gained in each evaluation are approximated by using the area under-the-curve technique. To gain insight into the uncertainty around the pooled mean ICUR, we will plot the pooled bootstrapped cost-effect pairs on cost-utility planes. Finally, acceptability curves will be presented which represent the probability that the intervention is cost-effective, given a varying threshold for the willingness to pay for each QALY gained. The robustness of the cost-utility results will also be tested by computing distinct sensitivity analyses. For instance, we will perform a per protocol analysis from which the FMS patients who do not attend at least 6 MBSR or FibroQoL sessions will be excluded.

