One of the main risks in this study may be dropouts. A sensitivity analysis using a per protocol strategy will be performed to determine the impact of the adherence to the protocol in both the MBSR and FibroQoL groups. This RCT is intended to be as naturalistic as possible, so prescribed drugs are permitted throughout the study. The effects of these drugs on clinical and biological outcomes may constitute another study limitation. However, no baseline differences among study arms regarding medical drugs are expected (due to randomisation) and sub-analyses evaluating the potential effects of the main pharmacological treatments (e.g., antidepressants) on the outcomes will be performed. Moreover, received pharmacological treatment may not be stable over time (e.g., initiating antidepressant treatment due to a depressive episode, changing principle/dose of other drugs due to variations in clinical symptoms, or starting individual therapy with a psychologist) so it is probable that some patients will be excluded from the study due to drastic changes in their treatment. Patients will be asked at post- and follow-up assessments for details about changes in medical treatment received and the clinicians will check the pharmacological treatment history in the patients’ clinical chart.

To our knowledge, this study represents the first attempt to detect structural and functional brain changes and inflammatory marker variations after MBSR in patients with FMS. Indeed, few studies have focused on exploration of the neural and inflammatory underpinnings of psychological treatments in chronic pain patients. We hope that our work will offer new advances in understanding the psychophysiological processes altered by mindfulness and their relationship with clinical outcomes. Understanding of how mindfulness changes these variables will in turn increase our understanding of the role of the brain and the immune system in FMS. Furthermore, determining FMS profiles according to psychological and brain/immune variables may also allow prediction of treatment response in patients with this diagnosis. Given that patients with FMS usually present comorbidities with psychiatric disorders (such as depression or anxiety) and other central sensitivity syndromes (such as chronic fatigue syndrome), the results from this study may have translational value.

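### The mediation analysis is specified only in patients who attended at least 6 of 8 sessions, so its arm effects lose the protection of randomisation

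*Protocol article*

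**What the plan says.** The Abstract and the end of the Background give mediation of long-term clinical outcome as the third aim. The section Mediational analyses sets out path models with treatment (MBSR versus FibroQoL, without TAU) as the independent variable. Pre-to-post change in the process variables is the mediator, and change from baseline to 12-month follow-up is the outcome. On this time ordering it says: "we are taking temporality into account, which increases the prospect of establishing conclusions about causality". It then fixes the population: "We will analyse the data of participants from the MBSR and FibroQoL treatments who receive a sufficient dose of the intervention", defined as "attendance at a minimum of 6 of the 8 weekly sessions". No other mediation population is named.

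The section Analysis of clinical efficacy uses a different population. Treatment effects there are estimated by intention to treat in everyone randomised, with multiple imputation.

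The same 6-session threshold appears once more, in Cost-utility analysis. There it is one example among several sensitivity analyses: a "per protocol analysis from which the FMS patients who do not attend at least 6 MBSR or FibroQoL sessions will be excluded". The Discussion also mentions a per-protocol sensitivity analysis, without restating the threshold.

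**The concern.** Randomisation makes the MBSR and FibroQoL groups comparable as allocated. It does not make the attenders of one programme comparable with the attenders of the other. Number of sessions attended is known only after allocation, and it can reflect prognosis, motivation and the burden of the programme. If these act differently in the two arms, the retained groups differ in prognosis before any treatment effect is considered.

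Three quantities in the path model depend on the arm comparison: the arm-to-mediator path, the direct effect and the total effect. All three lose their randomised basis. The total effect in attenders is also not the effect estimated in the efficacy analysis, so the direct and indirect parts would not add up to the result the trial reports. A statement about how MBSR works would then explain an effect in a different, selected group. Putting the mediator before the outcome in time does not repair this.

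**Working it through.** **Plan's own figure.** The protocol gives no attendance rate and no power or precision figure for the mediation analysis, so there is nothing to reproduce. The size can only be given as a range under assumptions.

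**Numbers analysed.** The plan has 60 patients per arm (Participants), so 60 + 60 = 120 in the two active arms. With attendance of 70% and 85% (assumed), 42 + 51 = 93 remain and 27 are dropped.

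**Could attendance differ by arm?** The documents point both ways. The note to Table 2 calls the two programmes structurally equivalent, each with eight 2-hour sessions. The note to Table 1 adds daily home practice of 30 to 45 minutes on 6 days a week and a day-long retreat for MBSR. No retreat is described for FibroQoL.

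**Selection formula.** Suppose no treatment effect, and a latent normal attendance tendency that correlates r with outcome. If a fraction p falls below the threshold, the mean outcome of the attenders shifts by r × φ(z_p) / (1 − p) SD.

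- p = 0.30: φ = 0.348, and 0.348 / 0.70 gives 0.497r
- p = 0.15: φ = 0.233, and 0.233 / 0.85 gives 0.274r
- Spurious difference between arms: (0.497 − 0.274)r, about 0.222r
- r = 0.3 gives 0.067 SD; r = 0.5 gives 0.111 SD
- Equal p and equal r in both arms give 0

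**Simulation.** A large-sample simulation set the true effect of arm on mediator and outcome to zero. Prognosis was assumed to correlate 0.5 with mediator change and 0.5 with outcome change. The first column is the correlation of attendance with prognosis in the two arms. The other values are in SD, among attenders only.

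| Correlation | Attendance | Arm to mediator | Total | Indirect |
|---|---|---|---|---|
| 0.5 / 0.5 | 80% / 80% | 0.00 | 0.00 | 0.00 |
| 0.5 / 0.5 | 70% / 85% | 0.06 | 0.06 | 0.01 |
| 0.5 / 0 | 80% / 80% | 0.09 | 0.08 | 0.02 |
| 0.5 / 0 | 70% / 70% | 0.12 | 0.12 | 0.03 |
| 0.5 / −0.3 | 70% / 80% | 0.18 | 0.18 | 0.04 |

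With all randomised patients included, every estimate in these five settings was within 0.003 SD of zero. The second row agrees with the formula: attendance and outcome are linked only through prognosis, so r = 0.5 × 0.5 = 0.25, and 0.222 × 0.25 = 0.056. Rows three and four show that equal attendance rates are not enough; the reasons for attending must also be alike.

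**The case against.** The strongest reply is that the causal remark is modest and concerns time ordering only. It comes before the attendance sentence and speaks of a better prospect, not of proof. That is a fair reading. It is also true that the mediator-to-outcome path is not randomised in either population, so including all 120 patients would not turn the mechanism question into a randomised comparison. Both points stand. They limit the claim to the arm-to-mediator, direct and total effects, but do not remove it. The spurious indirect effect, the quantity of most interest, is also small in the simulation, at 0.00 to 0.04 SD.

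A reader might go further in three ways that the documents do not support.

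- **That the per-protocol cost-utility run is an error.** It is offered as one sensitivity analysis beside the main one, which is acceptable as an adherence analysis. TAU has no sessions and stays unfiltered, so that comparison with TAU is not randomised. This calls for a note, not removal.
- **That dropout is not handled.** The Discussion says "One of the main risks in this study may be dropouts" and then turns to a per-protocol analysis, but gives its purpose as the impact of adherence. Missing outcomes are dealt with by intention to treat and multiple imputation, and further detail on imputation is commonly left to the analysis plan.
- **That the bias is a large share of the planning effect of d = 0.53, in favour of the active arms.** Larger shifts arise when filtered MBSR patients are set against unfiltered TAU, but TAU is not in the mediation analysis. The only per-protocol run with a stated threshold concerns costs and QALYs, for which d = 0.53 is not the yardstick. The direction is also an assumption.

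**Conclusion.** The point holds for the mediation analysis. The article states its population outright, so this is not detail deferred to another document. The choice conditions on a post-randomisation variable and departs from the intention-to-treat population used for efficacy.

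The spurious MBSR–FibroQoL difference is about 0.07 to 0.11 SD under assumed attendance of 70% and 85% and an attendance–outcome correlation of 0.3 to 0.5. It is zero if attendance works identically in both arms, and reached about 0.18 SD in the most adverse pattern simulated. All these inputs are assumed, and neither size nor direction can be fixed from the documents. The matter should be corrected because a stated objective rests on it.

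**What to change.** In Mediational analyses, define the main population as all patients randomised to MBSR and FibroQoL, analysed by allocated arm, with missing mediator and outcome values imputed as in the efficacy analysis. Keep the patients with at least 6 sessions as a sensitivity analysis, labelled as non-randomised. Say that the mediator-to-outcome path is observational in both.

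In Cost-utility analysis, keep the per-protocol run as a labelled adherence analysis and note that TAU is unfiltered, so the comparison with TAU is not randomised.

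The cost is revised wording and a few extra runs, with no new data. The downside is that low attenders may dilute the mediated effect; the labelled 6-session analysis shows by how much the estimate moves.
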